To examine the impact of the intervention, in the first 1-2 weeks following training, cohorts of children 5-15 years old will be recruited and screened using the parent report version of the Strengths and Difficulties Questionnaire (SDQ) that corresponds to the age of their child. The SDQ has been validated in Iran and yields measures of symptoms, functioning, and family burden plus overall scores and domain scores for hyperactivity and emotional, peer relationship, and conduct problems. In studies in other countries, the SDQ has been found to have similar or better sensitivity and specificity as the much longer CBCL (Goodman 1999). Screening results will not be shared with the GP, and summary scores will not be discussed with parents. Parents and children/youth will be free to discuss the screen with the GP or anyone else, and RAs administering the screens will encourage parents to discuss any concerns they have with their GP. Those children/youth who screen positive will be followed by telephone with re-assessment at 3 and 6 months after screening (regardless of whether or not the GP has considered them to have a mental health problem and entered them in the TUCCP registry).

The following figure is the currently planned timeline for the study, assuming recruiting of GPs in February-March, 2018 and beginning the trial in March-April, 2018.

| Study year          | 2016 7       | 2017 8       | 2018 9       | 2019  |
|---------------------|--------------|--------------|--------------|-------|
| month               | JASONDJFMAMJ | JASONDJFMAMJ | JASONDJFMAMJ | JASO  |
| Formative work      | XXXXXXXXXX   |              |              |       |
| Pilot training      |              | X XX         |              |       |
| Recruit GPs         |              | X            |              |       |
| GP group 1          |              | TRFF         | FFFFW        |       |
| GP group 1          |              | CRFF         | FFFF         |       |
| GP group 2          |              | TR           | FFFFFW       |       |
| GP group 2          |              | CR           | FFFFF        |       |
| GP group 3          |              |              | TRFFFFFW     |       |
| BP group 3          |              |              | CRFFFFFF     |       |
| Crossover trainings |              |              |              | T T T |

GP=general practitioners  

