As noted above, we will not share screening results with the GPs, though we will tell parents that they are free to talk with their GP about the screening and their answers. We have made this decision based on the pragmatic nature of this trial. Initiation of universal or even consistent indicated screening is technically challenging and, were we to be initiating it as part of the study, would not likely be continued. That would be a threat to the generalizability of our results. Future studies may be able to address the costs and benefits of routine screening being part of the support offered by participation in TUCCP.

Child/parent follow-up data collection. An abbreviated data set (the key mental health outcome measures – SDQ and GHQ) will be collected by telephone three months after the initial visit for both the control and intervention children/parents; a longer final data collection will occur at six months after the initial visit. We will only follow those families whose child screened positive on the SDQ at the index visit, or for whom the SDQ was negative but the GP entered the child in the TUCCP database. It will not be possible to guarantee that research assistants making follow-up calls will be blind to the child's control-intervention status because assistants who recruit families will, when possible, also make follow-up calls so that a known person is maintaining contact. However, the assistants will have no other information about the family other than what is reported on the study instruments. In particular, they will have no knowledge of any data about the child from the TUCCP database, and they will administer the SDQ and GHQ prior to instruments (at the baseline and final visit) that might reveal information about use of any mental health services. We believe that the families' familiarity with the research assistant, coming from an in-person contact at the time of consenting, will promote follow-up. We believe that this advantage balances out concern about biased outcome assessment.

The literacy rate varies among the families to be recruited, and we anticipate that some parents will require that the consent forms (and instruments if done in person) will be read to them. This will take place in private, and we will have a sufficient number of female research assistants so that there are no barriers to participation because of staff gender.

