| Anxiety                                              | Psychoeducation, active coping (role models, supported exposure, relaxation), support and response to maladaptive cognitions following trauma, exploration of contributing stresses, indications for medication.                                                                                                                 |
| Substance use                                        | Recognition of harmful use of tobacco, alcohol, and inhalants. Brief counseling regarding cessation.                                                                                                                                                                                                                             |

GPs assigned to the control arm of the study will receive a one-day child mental health update that will include role plays and practice recognizing child mental health problems. This will be a "booster" since similar trainings have been offered to GPs in the TUCCP in the past. As is

currently TUCCP policy, GPs will be instructed to refer all detected cases to the CMHC. At the end of the trial, all control GPs will be offered the intervention training.

GP data collection. The GPs will complete brief demographic and attitude surveys at the outset of the study and again at its conclusion. Both control and intervention GPs will complete very brief post-visit forms for enrolled patients indicating their assessment of whether a child has a mental health problem and, if so, their working diagnosis and treatment plan. They will also interact with two standardized patients portraying child mental health problems – one at the end of their training and once during the patient follow-up period.

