#### Assessments completed by GPs

| Instrument/assessment name                                 | Respondent | Timing/method of administration                                                      |
|------------------------------------------------------------|------------|--------------------------------------------------------------------------------------|
| Demographic data                                           | GP         | Baseline recruiting of GP                                                            |
| Confidence in treating common child mental health problems | GP         | Baseline recruiting of GP and end of intervention period                             |
| Confidence in treating common adult mental health problems | GP         | Baseline recruiting of GP and end of intervention period                             |
| Burden subscale, Physicians' Belief Scale                  | GP         | Baseline and end of intervention                                                     |
| GP visit exit questionnaire                                | GP         | At end of index visits for consenting parent/child pairs                             |
| Standardized patient visits                                | GP         | At end of initial training workshop and then once about midpoint of follow-up period |

GP follow-up interview: A small sample (10-15) of participating GPs will be approached for follow-up qualitative interviews either in person or as a focus group (this possibility will be included in their initial consent). The interviews will be scheduled at a time and place of the GP's convenience. The interviews will focus on the experience of providing care for child/youth emotional or behavioral problems and collaborating with the CMHC. A major goal of the interview will be to understand how the experience of training and working with the CMHC was able to build GP confidence in treating these problems and willingness to do so. These interviews will be recorded and transcribed for analysis.

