986 protocol, GPs may opt to treat or refer any patient. In addition, the impact of implementation  
987 outcomes such as GP changes in attitude and confidence (“post-treatment mediator” variables)  
988 will be examined using causal mediation methods [61].

989

990

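### GP attitude and confidence are planned as causal mediators, but on the natural reading of the schedule their only post-training measurement comes at or after the outcomes they would explain

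*Protocol*

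**What the plan says.** The closing sentence of the Protocol's Data analysis approach concerns implementation "outcomes such as GP changes in attitude and confidence (“post-treatment mediator” variables"; their impact, it says, "will be examined using causal mediation methods".

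The measurement of these variables is fixed in two places:

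- GP training, paragraph on GP data collection: "The GPs will complete brief demographic and attitude surveys at the outset of the study and again at its conclusion".
- Table of assessments completed by GPs: both confidence scales at "Baseline recruiting of GP and end of intervention period", and the Burden subscale of the Physicians' Belief Scale at "Baseline and end of intervention".

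The patient side is fixed as follows:

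- Study procedures: "in the first 1-2 weeks following training, cohorts of children 5-15 years old will be recruited and screened".
- Treatment and control interventions, on follow-up: the SDQ and GHQ "will be collected by telephone three months after the initial visit for both the control and intervention children/parents", and "a longer final data collection will occur at six months after the initial visit".

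**The concern.** A causal mediation analysis estimates how much of the effect of training on the outcome passes through a change in the mediator. That requires the mediator value to be settled before the outcome arises. Here the change in confidence spans the whole period over which the children are followed. A GP whose registered patients did well may end the study more confident for that reason. An association between final confidence and child outcome would then be read as training working through confidence, although the influence ran the other way.

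At stake is what the trial can say about how training works. The timing is set by the data collection schedule, so no statistical analysis plan can supply the missing measurement.

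**Working it through.** **1. Order of measurement.** The schedules, set side by side:

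| Time | GP attitude, confidence, Burden | Child SDQ, parent GHQ |
|---|---|---|
| GP recruiting | measured | none |
| End of training | none (first standardized patient only) | none |
| First 1-2 weeks after training | none | baseline |
| 3 months after index visit | none | measured |
| About mid follow-up | none (second standardized patient only) | none |
| 6 months after index visit, or later | measured (study's conclusion) | 6-month outcome |

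No attitude or confidence value is scheduled between training and the 3-month outcome. The single post-training value follows the 3-month outcome and coincides with or follows the 6-month outcome.

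**2. Inputs for size.** All are from the sample size text under Population and recruiting: SD 7.2, baseline-outcome correlation .37, correlation between outcomes .55, target difference 2.5, ICC .01, 45 GPs. The plan's own figure reproduces from them:

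- Variance factor: 1 + (1 + .55)/2 - 2(.37) = 1.035.
- n = 2 × (7.2/2.5)² × (1.960 + 0.842)² × 1.035 = 134.8, so 135 per arm.
- 270 × 1.05 = 283.5, so 284 at outcome, and 284/45 = 6.31 children per GP.

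**3. Spread of GP-level outcomes within an arm.**

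- Variance after adjusting for baseline: (1 - .37²) × 7.2² = .8631 × 51.84 = 44.74.
- Between-GP part at ICC .01: .01 × 51.84 = 0.52, an SD of 0.72.
- Sampling part of a GP mean: (44.74 - 0.52)/6.31 = 7.01.
- Observed GP mean: variance 0.52 + 7.01 = 7.53, SD 2.74. Sampling of about six children makes up 7.01/7.53 = 93% of this variance.

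**4. Spurious indirect effect with no true mediation.** Let a be the arm difference in confidence in SD units and rho the within-arm correlation of final confidence with how patients fared. The spurious effect is a × rho × (SD of what confidence tracks). Assumptions, not document figures: a = 1, rho = .2 to .4.

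- Confidence tracks the observed mean of the sampled children: .2 × 2.74 = 0.55 to .4 × 2.74 = 1.10 points, or 22-44% of 2.5.
- Confidence tracks only the between-GP component: .2 × 0.72 = 0.14 to .4 × 0.72 = 0.29 points, or 6-12% of 2.5.

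**5. Simulation, also on assumed inputs.** Setting: 45 GPs with 6 children each, ICC .01, total effect 0.34 SD, no true mediation, training raising confidence by 0.5 SD. Final confidence rose by 0, 0.2, 0.3 or 0.5 SD per SD of better observed GP mean. The apparent share mediated was about 0%, 16%, 25% and 44%. The mediator-outcome path was significant in about 5%, 26%, 47% and 87% of runs. This again lets confidence follow the observed mean, so it belongs with the larger range in step 4.

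**The case against.** Several points on the other side have weight.

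- **Objective 1 spells out its mechanisms differently.** It lists the conditions GPs identify and treat and the treatments families take up. The GP exit questionnaire and the TUCCP records cover these. A reader might infer that Objective 1 fails; the documents do not support that. Confidence mediation is one closing sentence, apart from the intent-to-treat comparison and the sample size. This stands and limits the scope.
- **The outcome of the mediation model is not named.** Objective 1 and the patient-outcome models make the child or parent outcome the natural reading, but it remains a reading. If the outcome were GP behaviour, such as identification at the index visit, much of that would also precede the final survey.
- **Other mediators are possible.** The sentence gives examples only. The standardized-patient visits precede the 6-month outcome, but they assess performance, not attitude or confidence.
- **The table's timing phrase is undefined.** Read alone, it could mean the end of training. The text on GP data collection points to the study's conclusion, and the same table uses a separate phrase for the training workshop. End of study is therefore the better reading, though not a certain one.
- **GPs may know little of how these children fared.** Screening results are withheld from them, follow-up SDQs are taken by research assistants by telephone, and control GPs are told to refer detected cases. A reader might infer that reverse influence is certain; the documents show only that it is possible. It is not ruled out, because GPs follow registered cases and receive feedback on them. The GP follow-up interviews also set out to learn how working with the CMHC built confidence.

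**Conclusion.** The point holds for a secondary mechanism analysis. On the natural reading of both the timing and the outcome, the schedule cannot support a causal reading of mediation through GP attitude or confidence, because the mediator does not precede the outcome.

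The documents do not determine the size of any bias. About 0.14 to 1.1 SDQ points, or 6-44% of the target, covers the assumed correlations of .2 to .4 and the assumed 1-SD arm difference. Where it falls depends on whether confidence follows only the between-GP component or the observed mean of the roughly six sampled children. A reader might take the 22-44% part alone as the expected bias. That is not supported, since it rests on a GP-mean SD that is mostly sampling noise. The conclusion itself rests on the order of measurement and would stand without these figures.

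**What to change.** Add the confidence and Burden scales once in both arms, after training and before the 3-month child outcome. The end of training, when the first standardized-patient visit takes place, is one suitable occasion. Use that score, adjusted for the recruiting score, as the mediator, and keep the end-of-study score as an implementation outcome. State which outcome the mediation model explains, and define the table's phrase for the final GP assessment.

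The cost is one short extra questionnaire per GP. A score at the end of training would miss confidence gained later through the booster session and work with the CMHC. A later occasion, still before the 3-month outcome, would capture more of that, but by then the GP may already have seen how some patients are doing. An earlier measurement restores the time order but does not remove confounding between mediator and outcome. If no such measurement is added, report the analysis as association and not as causal mediation.
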